#### Group b (Occiflex group): Occiflex + Home exercise + Booklet education

Patients in the Occiflex group will receive the standard home exercise programme and health education as group A combined with the computerised mobilisation (Occiflex) treatment. The Occiflex device can record any head and neck mobilisation in a 3D space as performed by the physiotherapist (Fig. 3a). The recorded mobilisation will be used as a template for repeated movement (Fig. 3b). The participants allocated to the Occiflex group will be divided into three categories according to their symptoms and a physical examination of their neck pain [7]: (a) neck pain with mobility deficits; (b) neck pain with headache (cervicogenic); and (c) neck pain with shoulder radiating pain (radicular). Individualised mobilisation will be determined for each category following three principles [18]: (a) stretching shortened or tight muscles; (b) mobilisation of facet joints relevant to pain; and (c) extending the limited range of motion based on the CROM examination. This mobilisation programme will be determined by an experienced physiotherapist during the first visit and performed using a computer afterwards. Each treatment session will last for 20 min and will be done every 3 days for a total of 10 times in 1 month.

**Fig. 3 Fig3:**
[figure not shown]
Computerized mobilisation using the Occiflex device. **a** Physiotherapist teaching the device individualized mobilisations; (**b**) Occiflex repeat the recorded mobilisation automatically

#### Group c (Manual group): Manual therapy + Home exercise + Booklet education

The participants in the manual group will receive the standard home exercise programme and health education combined with manual therapy based on the neck pain clinical practice guidelines. Similar to Group B, all participants in this group will be divided into three categories and treated with cervical and thoracic mobilisation accordingly [7]. The physiotherapist who performs manual therapy must be qualified and should have received the standardised training as described in *Maitland’s Vertebral Manipulation (7th edition)*. Each treatment will last for approximately 20 min and will be performed every 3 days for 10 times in 1 month. The manual therapy technique [21–23], which consists of three parts, is illustrated in Fig. 4.

**Fig. 4 Fig4:**
[figure not shown]
Manual therapy protocol. **a** Thoracic intervertebral joint mobilisation; (**b**) Cervical articular joint mobilisation; (**c**) Suboccipital muscle stretching

Thoracic intervertebral joint mobilisation. The patient lies prone with his/her forehead resting on his/her hands. The therapist will place a pad of his/her thumbs in a spinous process to rhythmically apply pressure to the vertebra from T1 to T4 separately, usually in a posterior-to-anterior direction. The thumbs may be positioned tip to tip or with the tips side by side to transmit the oscillating pressure from body weight to the hand. This mobilising technique will be carried out 2 min for each intervertebral joint.Cervical articular joint mobilisation. The physiotherapist will palpate the neck to find the two or three most dysfunctional joints from C2 to C7 and then use his/her thumbs to perform passive joint mobilisations to those joints. The oscillatory pressure will be directed postero-anteriorly against an articular process at a speed of 1 to 2 Hz for 3 min each according to irritability of the patient’s disorder.Suboccipital muscle stretching. The patient lies supine with his/her head in a neutral position. The physiotherapist places one supinated forearm underneath the patient’s neck with the other hand fixing the chin. The contact forearm then pronates against the patient’s occiput and sustains the force for 30 s to stretch the suboccipital muscle. This technique can be repeated 3 times as required.

### Outcome measures

Personal information, including age, gender, BMI, international physical activity questionnaire (IPAQ) [24], working years and time since the onset of symptoms, will be collected at the baseline. The primary outcome measurements will include the VAS for pain and NDI to be administered at weeks 4 and 12. Secondary outcomes will include CROM, pressure pain threshold (PPT), global perceived effect (GPE) and sick leave. These evaluations will be carried out by an evaluator trained with these procedures. The adverse reactions during therapy will also be recorded.

#### Visual analogue scale (VAS) for pain

The participants will be asked to indicate the intensity of their neck pain during the last week on a 10 cm horizonal scale, where 0 means no pain and 10 means unbearable pain [25]. The minimal clinically important change values range from 2.5 to 4.9 points for patients with neck pain, and an improvement below 1.5 points can be interpreted as irrelevant for pain intensity [26]. The VAS will be obtained at the baseline, week 4 and week 12 of the study period (post-treatment and 3 months follow up).

#### Neck disability index (NDI)

The NDI is often used for a self-assessment of the cervical spine function of neck pain patients with validity and reliability [27]. This index consists of 10 questions covering different aspects of the patients’ daily life activities. Each item is rated on a scale of 0 to 5, where 0 means ‘no pain’ and 5 means ‘unbearable pain’. A higher score indicates greater disability. The clinically important difference for NDI is approximately 5 points to demonstrate treatment benefits after intervention [28]. The NDI will be measured at the baseline, week 4 and week 12 of the trial.

#### Cervical range of motion (CROM)

CROM refers to the angle of motion when the neck moves in a certain direction, which is an indicator for assessing the motion of the neck. Cervical range-of-motion device (CROM; Performance Attainment Associates, Lindstrom, MN) provides a clinical tool for accurately measuring CROM, including flexion, extension, side bending and rotation in sitting position, with high intraclass correlation coefficients (ICC) ranged from 0.88 for flexion (95% CI: 0.73–0.95) to 0.96 for left rotation (95% CI: 0.91–0.98) [29]. The CROM will be measured at the baseline, week 4 and week 12 of the study period.

#### Pressure pain threshold (PPT)

The PPT is recorded using the digital algometer FPX-25 (Wagner Instruments, Greenwich, CT) to measure the midpoint of the bilateral trapezius muscle and the spinous process of the vertebra C2 [30]. The therapist gradually increases the pressure until the participant complains of pain or discomfort. PPT has reported high intra- and inter-rater reliabilities (ICC = 0.94–0.97; ICC = 0.79–0.90, respectively) amongst patients with neck pain[31]. The measurement should be repeated three times, and the average scores should be computed. The PPT will be assessed at the baseline, week 4 and week 12 of the study period.

#### Global perceived effect (GPE)

The GPE provides physicians with a reference on the overall recovery condition of their patients. GPE scales are commonly advocated for use in chronic pain research and clinical practice[32]. In this scale, ‘5’ indicates that the neck pain deteriorates to the greatest extent, whereas ‘5’ indicates complete recovery. The GRE will be assessed at weeks 4 and 12 of the study period.

#### Sick leave

Sick leave was measured three months after the baseline by asking the participants: ‘How many times were you absent from work because of neck pain since the last treatment?’ [33]. The length and frequency of sick leaves will be recorded for comparison.

### Sample size calculation

The sample size will be calculated using PASS 15.0.5 based on the means, standard deviations and an alpha of 5% (0.05) with a unilateral contrast. Assuming that the standard deviation of NDI scores is 8, then 38 participants per group will give the study 80% power to detect minimum clinically important differences (MCID) of 5 units in NDI [34]. Meanwhile, 41 participants per group are required based on the 10 cm VAS scale with a standard deviation of 5 and a clinically significant difference of 3 points [26]. To accommodate an expected dropout rate of 20% during follow-up and to have sufficient statistical power for the different variables in this study, a total of 150 participants will be sufficient.

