### Statistical analysis

The statistical analysis will be carried out using the IBM SPSS Statistics 26 software. Descriptive statistics will be used to describe the study population and will be summarised per group based on the number of observations, means and standard deviations. The primary and secondary outcome variables (VAS, NDI, CROM, PPT and GPE) will be analysed by intention to treat and by using linear mixed models with repeated measures. The linear mixed model requires the residuals to be normally distributed. The Shapiro–Wilk test will be applied to test the normality. In case of a non-normal distribution of the residuals, an appropriate non-parametric test will be conducted. Multiple post-hoc comparisons will be conducted through Bonferroni’s contrast for parametric distributions. All tests will be two sided, and the level of significance is set to 0.05. The missing data in this study will be handled with a mean imputation or mixed modelling approach.

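### The stated 80% power rests on a one-sided test without multiplicity correction, whereas the analysis is two-sided with Bonferroni, and the printed sizes do not follow from their inputs

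*Protocol article*

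**What the plan says.** Under Sample size calculation, the article plans with "an alpha of 5% (0.05) with a unilateral contrast". For NDI it gives "Assuming that the standard deviation of NDI scores is 8" and concludes that "38 participants per group will give the study 80% power to detect minimum clinically important differences (MCID) of 5 units in NDI". For VAS it gives 41 per group, from an SD of 5 and a difference of 3 points; power is not restated there. It then arrives at 150 in total, with this reason for the margin: "To accommodate an expected dropout rate of 20% during follow-up". Randomisation is equal across three arms, so 150 is 50 per arm.

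Under Statistical analysis, the article says "All tests will be two sided, and the level of significance is set to 0.05", and "Multiple post-hoc comparisons will be conducted through Bonferroni’s contrast for parametric distributions". The number of comparisons in the Bonferroni family is not given.

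Under Objective, the hypotheses are between-arm contrasts: computerised mobilisation better than manual therapy, and better than exercise alone.

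**The concern.** The two sections state different tests. A one-sided 5% test needs fewer participants than a two-sided one, and the sample size section makes no allowance for a multiplicity correction that falls on the contrasts the trial exists to estimate. If 80% is carried into the report, a reader will take the chance of missing a true 5-point NDI difference to be 20%. A non-significant Occiflex-versus-manual result could then be over-read, in a trial whose Discussion asks whether Occiflex can serve as an alternative. Leaving both rules in print also leaves the sidedness of the final test open to choice.

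**Working it through.** **Inputs.** From Sample size calculation: NDI difference 5, SD 8 (ratio 0.625); VAS difference 3, SD 5 (ratio 0.6); alpha 0.05 one-sided; power 80% (assumed to apply to VAS as well); dropout 20%; total 150. From Statistical analysis: two-sided 0.05 with Bonferroni. Assumed: a Bonferroni family of two or three pairs, giving 0.05/2 = 0.025 or 0.05/3 = 0.0167 per comparison.

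**Step 1: reproduce 38 and 41.** Normal approximation: n per group = 2(z_alpha + z_power)² × SD²/difference².

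- NDI, one-sided 5%, 80%: 2 × (1.645 + 0.842)² × 64/25 = 31.7, so 32. The exact t-test gives 33.
- VAS, one-sided 5%, 80%: 2 × (1.645 + 0.842)² × 25/9 = 34.4, so 35. The exact t-test gives 36.

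The printed 38 and 41 are not reproduced. Other readings (exact test):

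| Test | NDI n | VAS n |
|---|---|---|
| One-sided 5%, 80% power (as stated) | 33 | 36 |
| One-sided 5%, 85% power | 38 | 41 |
| Two-sided 5%, 80% power | 42 | 45 |
| Two-sided 0.05/2, 80% power | 50 | 55 |
| Two-sided 0.05/3, 80% power | 56 | 60 |
| Three-arm F test, one arm shifted, 80% power | 39 | 42 |

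The printed sizes match 85% one-sided power exactly. They also come close to the three-arm F test (power 79.98% at 38 and 79.83% at 41), but that test is not one-sided and does not target one pairwise difference. Which of the two was used cannot be told from the article.

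**Step 2: dropout.** 50 × (1 − 0.20) = 40 completers per arm. This exceeds 38 for NDI but is one short of 41 for VAS. Inflating correctly, 41/0.80 = 51.25, so 52 per arm and 156 in total. The printed 150 fits 41 × 1.2 = 49.2, rounded up to 50 per arm.

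**Step 3: power at 40 completers per arm.** Two-sample t-test, 78 degrees of freedom, noncentrality = difference/(SD × √(2/40)): 5/(8 × 0.2236) = 2.795 for NDI and 3/(5 × 0.2236) = 2.683 for VAS.

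| Two-sided test | NDI power | NDI difference detectable at 80% | VAS power (SD 5) |
|---|---|---|---|
| Single contrast, 0.05 | 78.8% | 5.1 | 75.5% |
| Bonferroni, two pairs | 69.4% | 5.6 | 65.5% |
| Bonferroni, three pairs | 63.7% | 5.9 | 59.5% |

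With no dropout (50 per arm), NDI power is 87.2%, 80.0% and 75.3% in the same order.

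**Step 4: split the loss.** Moving to two-sided 5% leaves NDI at 78.8%, about one point below the stated 80%, because 40 completers is more than a one-sided 80% test needs. Bonferroni for three pairs then takes a further 78.8 − 63.7 = 15.1 points.

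**Step 5: baseline adjustment.** If the model uses the baseline value, the SD becomes SD × √(1 − r²), where r is the baseline-to-follow-up correlation. The article gives no r. Three-pair NDI power at 40 per arm is about 69% at r = 0.3, 78% at r = 0.5 (SD 8 × 0.866 = 6.93) and 93% at r = 0.7.

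**The case against.** The strongest reply has four parts.

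- **Sidedness is nearly harmless for NDI.** At 40 per arm a single two-sided contrast has 78.8% power. This stands, and the one-sided wording on its own should not be presented as a large loss of power.
- **The large loss depends on a family size the article does not state.** This also stands. Three arms suggest three pairs, but a full analysis plan may name two pairs or one primary contrast, and the post-hoc tests may follow a group-by-time test. Hence the range above.
- **The planned analysis is a repeated-measures mixed model, not a t-test at one time point.** Baseline data could recover power, and participants who leave after week 4 would still contribute, so 40 per arm is a cautious count. This stands as a qualification. It does not rescue the printed 80%, because the article claims no such gain and states no correlation.
- **The VAS figures reflect an SD of 5, the largest possible on a 0–10 scale.** This stands. With an SD of 4, three-pair power at 40 per arm is 82%; with 3, it is 98%. VAS is therefore weak evidence of a shortfall.

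A reader might infer that the trial has only 64% power, or that it must enrol 210 or more (56/0.8 = 70 per arm for NDI). The documents do not support either: both require three pairs and an unadjusted analysis. The dropout shortfall is one participant per arm, for VAS only.

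**Conclusion.** The point holds as an internal inconsistency with a conditional effect on power. Three things are wrong as written: the two sections disagree on sidedness and the sizing ignores the Bonferroni step; 38 and 41 do not follow from the stated alpha and power; and 150 less 20% falls one per arm below the stated VAS requirement.

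On the protocol's own NDI inputs with 40 completers per arm, an unadjusted two-sided test has between 63.7% and 78.8% power, depending on whether three pairs, two pairs or one contrast is tested. The corresponding detectable difference is 5.9 to 5.1 points, against the 5 that the article treats as clinically important. The range rests on an assumed family size and no gain from baseline. With a baseline correlation of 0.5 (assumed), three-pair power is about 78%; with 0.7, it exceeds 80%. The supportable conclusion is that the 80% is not backed by the calculation shown, not that true power is known to be far below it.

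**What to change.** 1. Use a two-sided alpha of 0.05 in Sample size calculation, to agree with Statistical analysis.
2. State either one primary contrast (for example Occiflex versus manual therapy) at two-sided 0.05, or the Bonferroni family and its size.
3. Replace 38 and 41 with the sizes that follow from the chosen test, and inflate for dropout by dividing by 0.80.
4. Restate power and detectable NDI difference at 40 completers per arm for that test. Without baseline adjustment these are about 79% and 5.1 points (one contrast), 69% and 5.6 (two pairs) or 64% and 5.9 (three pairs). If baseline adjustment is relied on, state the assumed correlation and show a range.
5. Say that the VAS figure depends on the assumed SD of 5.

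The cost is rewording one section and a less favourable stated power. No added enrolment is needed. Settle it before the outcome data are analysed, so that the sidedness and the family are not chosen afterwards.

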**Fig. 1 Fig1:**
[figure not shown]
Flowchart of research protocol

**Table 1 Tab1:** Inclusion and exclusion criteria

Inclusion criteria
**• **Age: 18 and 55 years • Office workers performing at least 4 h of computer work per day (on average) • Current neck pain, with or without pain in head or arm region • Experiencing pain for least 3 months, at a moderate or high pain intensity (≥ 5 of 10, Visual Analog Scale) • No cognitive impairment and volunteer to participate in the study
Exclusion criteria
• Pain caused by definite pathological factors, such as cerebrovascular diseases involving vertebral arteries, spinal cord pathology, cervical cancer or fracture • Neck pain secondary to diseases such as rheumatoid arthritis, ankylosing spondylitis and cervical spine infection • Suffering from cervical myelopathy or radiculopathy, coupled with motor, reflex, and/or sensory changes in the upper limb • Recurrent vertigo, or dizziness • Previous surgery to the cervical spine

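### The VAS sample size rests on an SD of 5 that a 0–10 scale cannot produce alongside a 3-point group difference; NDI is the outcome that limits power

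*Protocol article*

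**What the plan says.** VAS pain and NDI are both primary outcomes, measured at weeks 4 and 12 (Outcome measures). The Sample size calculation section treats each in turn:

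- **NDI:** SD 8, difference 5; "38 participants per group will give the study 80% power".
- **VAS:** "41 participants per group are required based on the 10 cm VAS scale with a standard deviation of 5". The effect to be detected is put at 3 points.
- **Error rate:** "an alpha of 5% (0.05) with a unilateral contrast".
- **Total:** 150 participants, allowing for 20% dropout.

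The section on the VAS defines it as a "10 cm horizonal scale, where 0 means no pain and 10 means unbearable pain". Table 1 admits patients with pain "at a moderate or high pain intensity (≥ 5 of 10, Visual Analog Scale"). The Statistical analysis section says "All tests will be two sided, and the level of significance is set to 0.05", and gives Bonferroni post-hoc comparisons.

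**The concern.** An SD of 5 on a scale 10 points wide describes a group in which half the patients report no pain and half report the worst possible pain. No trial population looks like that. Because the resulting 41 exceeds the 38 for NDI, the text makes the VAS look like the more demanding outcome and the one that fixes the trial's size. A reader could then assume that NDI, needing fewer patients, is comfortably covered. The stake is the accuracy of the stated power for two primary outcomes: it is understated for the VAS, and the thinner margin on NDI is hidden.

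**Working it through.** **1. Reproducing 41 and 38.** Inputs from the Sample size calculation section: VAS difference 3, SD 5; NDI difference 5, SD 8; alpha 0.05; power 80% (stated for NDI, assumed to apply to the VAS).

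| Method | VAS | NDI |
|---|---|---|
| Two-group t-test, one-sided 5%, 80% power | 35.04 → 36 | 32.35 → 33 |
| Two-group t-test, two-sided 5%, 80% power | 44.6 → 45 | 41.2 → 42 |
| Three-group one-way ANOVA, two means equal and one apart, 80% power | 41.16 | 38.01 |
| Two-group t-test, one-sided 5%, 85% power | 40.6 → 41 | 37.5 → 38 |

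The one-sided contrast at 80% power, as described, does not give 41 or 38. Two unstated methods match both figures. So 41 can be reached from SD 5, and the problem is the input.

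**2. What SD the scale allows.** A score between 0 and 10 with mean m has variance of at most m(10 − m).

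- One group: the maximum is at m = 5, where 5 × 5 = 25, so SD = 5. This needs half the scores at 0 and half at 10. A uniform spread over the whole scale gives 10/√12 = 2.89.
- Two groups with means m and m + 3: the average variance is at most [m(10 − m) + (m + 3)(7 − m)]/2. This is largest at m = 3.5, where both terms equal 3.5 × 6.5 = 22.75. The shared SD is at most √22.75 = 4.77.

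SD 5 and a 3-point difference therefore cannot both hold for raw scores.

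**3. How 41 leads to 150.** The steps are not shown, but 41 × 1.2 = 49.2, rounded to 50, and 50 × 3 = 150. Losing 20% of 150 leaves 120, or 40 per group.

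**4. Which outcome limits power.** The standardised difference is 5/8 = 0.625 for NDI and 3/SD for the VAS. The VAS is the more demanding only if its SD exceeds 3/0.625 = 4.8. The ceiling from step 2 is 4.77. So NDI is the more demanding for any VAS SD that raw scores can have at that difference, whatever value is assumed.

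**5. VAS at feasible SDs.** The protocol gives no alternative SD, so 2 to 3 is an assumption. Two-sample t-test, difference 3:

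| SD | n per group, two-sided 5%, 80% power | n per group at 0.0167 | Power with 40 per group, two-sided 5% |
|---|---|---|---|
| 2 | 9 | 11 | >99.9% |
| 2.5 | 12 | 17 | >99.9% |
| 3 | 17 | 23 | 99.3% |

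As a VAS requirement, 41 is too large by a factor of 41/17 = 2.4 to 41/9 = 4.6.

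**6. NDI with 40 completers per group.** Two-sample t-test, SD 8, difference 5: 78.8% power two-sided at 5%, and 63.7% at 0.05/3 = 0.0167, which assumes three pairwise comparisons. One-sided at 5% it would be 87.0%.

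**The case against.** Four objections carry weight.

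- **The 41 is not a miscalculation.** This stands. The two per-group figures fit a common method, which the text does not name. A reader might infer that 41 is an arithmetic error; the documents do not support that.
- **The error is on the safe side.** This stands. Too large an SD inflates the sample and costs no VAS power, and once NDI is taken as the driver the trial stays near 40 completers per group.
- **SD 5 might describe change scores.** This cannot be excluded. With entry at 5 or more, change could span about 15 points (from −5 to +10), so the ceiling of 5 would not apply, and at 3/5 = 0.6 the VAS would be slightly more demanding than NDI. But the sentence attaches the SD to the scale and says nothing about change, so that reading would have to be stated and sourced.
- **The entry criterion is not decisive.** This stands. A range of 5 to 10 would cap the SD at 2.5 at baseline, but the outcomes are read at weeks 4 and 12, when the cap no longer applies. The bound in step 2 does not use it.

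Two stronger readings are tempting. One is that the VAS figures have no meaning at all. That goes too far: the 3-point difference lies inside the 2.5 to 4.9 range that the protocol gives for important change, and only the SD is at fault. The other is that the trial will declare trivial VAS differences significant, since the protocol says "an improvement below 1.5 points can be interpreted as irrelevant for pain intensity". That does not follow from the SD, because the number of completers is about the same with or without the correction. The protocol's 1.5 and 2.5 to 4.9 thresholds also describe improvement in patients and not a difference between groups, so they give no ready rule for judging a between-group confidence interval.

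**Conclusion.** The point holds as a fault in a planning input. For raw scores, an SD of 5 is the ceiling of the scale and is incompatible with the 3-point difference used beside it, so 41 per group does not stand as a VAS requirement. That conclusion needs only the 0–10 bounds and the stated difference. That NDI is the limiting outcome follows from the same bound and the stated NDI inputs. The size of the overstatement, about 2.4- to 4.6-fold, rests on the assumed SD of 2 to 3.

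The consequence is modest. VAS power is higher than the protocol implies. NDI power with 40 completers is about 79% for a two-sided 5% test and about 64% if three pairwise comparisons are each tested at 0.0167. These are unadjusted comparisons at a single time point; a mixed model that uses the baseline and repeated measures could do somewhat better. The validity of the trial is not threatened. This is a correction worth making, not one on which the trial depends.

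**What to change.** In the Sample size calculation section:

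1. Replace the VAS SD of 5 with a feasible value and cite its source; or, if 5 is an SD of change, say so and cite that source.
2. Restate the VAS power for the 3-point difference with the expected completers.
3. State the test, sidedness and power that produced 38 and 41.
4. Name NDI as the outcome that sets the size (if the VAS SD is for raw scores), and restate its power for the two-sided tests of the Statistical analysis section, both at 5% and at the Bonferroni level.

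The cost is a few sentences and finding a source for the SD. Enrolment stays at 150.
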